#### Avoidance

##### Child avoidance measure self-report (CAMS, [62])

The CAMS contains eight items measuring a child’s tendency to avoid stimuli that elicit anxiety, fear, or worry (or: avoidance behavior, AB). The questionnaire presents a stem statement (When I feel scared or worried about something …) and the items covering various approaches to avoiding anxiety provoking stimuli, through passive and active avoidance, as well as refusal, (e.g., I try not to go near it). Items are rated on a Likert-type scale from Almost Never to Almost Always). The CAMS has good internal and test-retest reliability, concurrent and criterion validity, and treatment sensitivity. For the current study, the CAMS was translated to Dutch via a translate and back-translate procedure. One of the subgoals of this study is to psychometrically validate the Dutch version of the CAMS.

#### Child’s level of abstract reasoning

We measure the level of the children’s abstract reasoning skills to get an indication of the level of cognitive level (CL). We developed the abstract reasoning task ourselves to enable implementation in our online platform and enable a non-invasive adaptation specifically for our age group. Our abstract reasoning task is based on other freely available online abstract reasoning tasks and on the abstract reasoning task of the Matrix Reasoning of the fifth version Wechsler Intelligence Scale for Children (WISC-V, [63]). There are 10 tasks in which the child sees an array of abstract forms with one missing form. The child then has to select the correct form out of four alternatives.

### Analyses

Both the Statistical Packages for Social Sciences (SPSS, version 24) and R (R. C. Team, 2013) will be employed for performing the analyses. Multilevel analysis [64] is used to answer the various sub-questions. The study design is a randomized two-group factorial design with repeated measures of the dependent variables. Intervention versus control group makes the between subjects factor and time is the only within subjects factor. Alternatively, the design can be seen as a randomized two-group multilevel design with repeated measurements nested within subjects. The sub-questions correspond with different parameters to be estimated in the statistical model. The model can be seen as a moderated mediation [65] model in which the effect of the training is on the one hand by reducing dysfunctional cognitions and on the other hand by reducing avoidance. In addition, the path depends on the level of development of the child by reducing dysfunctional cognitions (see Fig. 1).

To test the primary research question, we will use regression model with the outcome Anxiety Level (AL) as dependent variable and condition (LTD vs WL) as predictor. Sex and Age will be added as extra predictors, plus interactions between predictors to see if the effects differ per sex and age category (LC). Model: AL = b0 + b1*Group + b2*Sex + b3*LC + b4*Group*Sex + b5*Condition*LC. To test the moderation and mediation models, we will use multilevel analysis [64]. The five assessments (T1,T2,T3,T4,T5) will be the lowest level, the children the second level. This model can be considered a moderated mediation model (Hayes, 2013). The mediation analysis will consist of 2 steps. 1st: Dysfunctional Cognitions (DC) and Avoidance Behavior (AB) will be dependent variables, in separate analyses. 2nd: Anxiety level (AL) will be the dependent variable. Time will be added and modelled as T = 0,1,2,3,4, to tested the linear increase of Anxiety Level (AL) during the intervention. We will use a random intercept model, because we expect individual differences to exist in the levels of DC, AB, AL. Step 1. DC = b0 + b1*Group + b2*Time VG = b0 + b1*Group + b2*Time. Step2. AL = b0 + b1*Group + b2*VG + b3*DC. To test the third hypothesis (moderation by cognitive level), we will perform a multilevel analysis as above. 1st: Dysfunctional Cognitions (DC) and Avoidance Behavior (AB) will be dependent variables, in separate analyses. Cognitive Level (CL) will be added as predictor in a hierarchical linear multilevel model, including the interaction with condition to test for the moderating effect of CL on the relation between condition and mediators. Time will be added and modelled as T = 0,1,2,3,4, to tested the linear increase of DC and AB during the intervention. We will use a random intercept model, because we expect individual differences to exist in the levels of DC and AB. DC = b0 + b1*Group + b2*CL + b3*Group*CL + b4*Time VG = b0 + b1*Group + b2*CL + b3*Group*CL + b4*Time. The variable Cognitive Level (CL) will be centered at zero. For the follow-ups, when interaction effects appear to be significant, simple slopes plots will be made to illustrate the interaction effect. The 95% confidence interval of the parameter estimates of the multilevel and logistic regression analyses will be used to assess the statistical and practical significance of the estimates. The standardized parameter estimates will be used as estimated effect sizes. For all interval variables univariate outlier detection will be applied by using the Inter Quartile Range (IQR): scores outside 1.5*IQR will be examined, in order to see whether these are genuine scores, and cannot be attributed to coding or other errors. If they are genuine the scores remain in the analysis, otherwise they are removed from the analysis. Since we will use multilevel analyses drop-outs can be kept in the analysis. Subjects with at least one wave (time point) with complete data will be used in the analysis. No imputation strategy will be applied. We will explore the time factor in more detail. Other coding schemes than a simple linear coding will be tested to see whether effect gradually weaken in time or take effect after a certain period. Furthermore, we will explore whether the proposed model has predictive value for the binary outcome (anxiety diagnosis).

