### Participants

We aim at recruiting children aged 8–13 years with high levels of anxiety, specific phobias or other mild anxiety disorders that are included in the fifth edition of the Diagnostic and Statistical Manual of Mental Disorders (DSM-5): social anxiety disorder, separation anxiety disorder, generalized anxiety disorder, panic disorder, selective mutism, agoraphobia. With mild we mean that the disorder does not strongly interfere with daily functioning, or, in other words, does not have a high severity. By performing a simulation study with 500 replications [52] with the package “lme4” [53] in R (R Core Team, 2013), we calculated how many children from this population should be included in our sample. For this simulation we assumed a medium direct effect of the training, a small effect of the indirect pathways via the mediators and 10% random drop-out between measurements. To assess the effect of the intervention, we include a waitlist control group in addition to the intervention group. In order to obtain 80% power of the direct and indirect pathways, we need a total sample size of 240 (120 children in the intervention group and 120 children in the waitlist control group). In principle, the inclusion of participants will continue until we reach this number. We exclude children with severe anxiety diagnoses, as determined by a trained clinician during a diagnostic interview. No further exclusion criteria are applied. We will recruit our participants via the community (i.e., non-clinical/ non-refferred) in the Netherlands, a list of study sites can be obtained via the first author.

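### The primary efficacy question is given a regression with no child level, contradicting the plan's own multilevel design and missing-data rules; no single-level version is both valid and consistent with them

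*Protocol article*

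**What the plan says.** All references are to the protocol article.

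- **Primary question (Analyses).** "To test the primary research question, we will use regression model with the outcome Anxiety Level (AL) as dependent variable and condition (LTD vs WL)" (the predictor), followed by "Model: AL = b0 + b1*Group + b2*Sex + b3*LC + b4*Group*Sex + b5*Condition*LC". There is no Time term, and no assessment is named as the source of AL.
- **Other questions (Analyses).** Immediately afterwards: "To test the moderation and mediation models, we will use multilevel analysis [64]", then "The five assessments (T1,T2,T3,T4,T5) will be the lowest level, the children the second level". The random intercept is introduced in this context.
- **Design (Analyses, opening paragraph).** "Alternatively, the design can be seen as a randomized two-group multilevel design with repeated measurements nested within subjects". The same paragraph says that multilevel analysis answers the sub-questions.
- **Missing data (Analyses).** Drop-outs are kept in because multilevel analyses will be used. "Subjects with at least one wave (time point) with complete data will be used in the analysis", and nothing is imputed.
- **Inference (Analyses).** Significance is judged from 95% intervals of the multilevel and logistic regression analyses.
- **Sample size (Participants).** "By performing a simulation study with 500 replications [52] with the package “lme4” [53] in R (R Core Team, 2013"), for 80% power on the direct and indirect pathways with 240 children and 10% random drop-out between measurements.

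**The concern.** Children are randomised individually and anxiety is measured at every one of five assessments. The order of the Analyses text gives the child level to the mediation and moderation models and leaves the primary efficacy question with a plain regression. The general rules later in the section presuppose a multilevel model and are not limited to the secondary questions.

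An analyst following the text must therefore break part of it. Using one wave drops children the plan says it keeps, and requires choosing a wave that the article does not fix. Using all waves without a child level treats up to 5 × 240 = 1,200 correlated scores as independent. Group is constant within a child, so the repeated scores add little information about it and its standard error would be too small. The trial's main efficacy claim rests on this test.

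**Working it through.** **Inputs from the article:** 120 children per arm; five assessments; 10% random drop-out between measurements; the six-term primary equation; a 5% two-sided level, implied by the 95% intervals. **Input not in the article:** the within-child correlation ρ of anxiety scores, taken here as 0.3 to 0.8 and equal for all pairs of waves.

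**The plan's own figure.** The 240 cannot be reproduced, because the simulation's coefficients, variances and correlation are not given. For orientation only: a medium effect taken as d = 0.5 needs 63 per arm in a two-group comparison. Power is 97% at 120 per arm and 88% at 79 per arm. The 240 is therefore presumably driven by the small indirect effects.

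**Reading A: single-level, one wave.** The Procedure section places assessments after sessions 1, 3 and 5, at the end of training and at follow-up, taken here as T1 to T5.

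- Retained at T4: 0.9^3 = 0.729, so 27% are lost (120 × 0.729 = about 87 per arm left).
- Retained at T5: 0.9^4 = 0.656, so 34% are lost (120 × 0.656 = about 79 per arm left).
- Simulated type I error of the six-term model on one wave under no effect: 4.7% to 5.0%, which is nominal.

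The test is valid, but it excludes children whom the at-least-one-wave rule includes.

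**Reading B: single-level, all waves pooled.** For a between-child effect, the variance is understated by DE = 1 + (E[m²]/E[m] − 1)ρ, where m is the number of waves a child contributes. With 10% loss per interval, m = 1 to 5 has probabilities 0.1, 0.09, 0.081, 0.0729 and 0.6561. Then E[m] = 4.095, E[m²] = 18.758 and DE = 1 + 3.581ρ. With complete data, DE = 1 + 4ρ. The actual error rate is 2(1 − Φ(1.96/√DE)).

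| ρ (assumed) | DE, drop-out | Error rate, formula | Error rate, simulated | Formula, no drop-out | Same equation with child random intercept, simulated |
|---|---|---|---|---|---|
| 0.3 | 2.07 | 17.4% | 16.6% | 18.6% | 4.8% |
| 0.5 | 2.79 | 24.1% | 24.2% | 25.8% | 5.1% |
| 0.7 | 3.51 | 29.5% | 29.0% | 31.5% | 4.8% |
| 0.8 | 3.86 | 31.9% | 32.1% | 33.9% | 5.4% |

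Simulations used 4,000 trials per setting with no treatment effect. The standard error of Group would be too small by a factor of √2.07 = 1.44 to √3.86 = 1.97.

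**Reading C: two-level.** Assessments nested in children with a random intercept use every child with at least one wave, fit the stated reason for keeping drop-outs, supply an interval from a multilevel analysis and match the design description. This is the only reading that fits all the general rules, but it is not what the primary-question sentence says.

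**Time.** Even in a two-level form, the printed equation has no Time term, so b1 would average the group difference over T1 to T5. T1 falls after psycho-education and before the exposure and cognitive restructuring components, so that average mixes an early assessment with those after the intervention.

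**The case against.** The strongest counter-case is that the article never calls the primary regression ordinary, single-level or pooled, and never says five waves enter it. With no Time term, a regression on one assessment is at least as natural a reading, and its error rate is nominal. The at-least-one-wave rule follows a sentence justifying it by multilevel analysis. If the rule covers the primary analysis, that analysis is multilevel; if it does not, the rule is no evidence of pooling. The printed equation proves little, because the multilevel equations also show only fixed terms and the second-step mediation equation also lacks Time. The lme4 sizing targets direct and indirect pathways, so it need not conflict with a one-wave primary test. A more detailed preregistered plan exists and is not shown.

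Most of this stands. A reader might infer that the planned primary analysis has a false-positive rate of 17% to 32%, or that its standard error is wrong whichever waves are used. The documents support neither. The first needs pooling, which is not stated, and a correlation that is not given. The second is false, because one wave per child gives a correct test.

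The contradiction remains. The missing-data and interval rules are written without restriction, and the primary question is the only linear analysis to which the text assigns a different model class. Confining those rules to the secondary questions would leave the main efficacy test outside the plan's own rules for drop-outs and inference. The existence of a fuller plan does not reconcile statements that conflict within the article.

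**Conclusion.** The point holds as an internal contradiction about the primary analysis model. It does not establish an inflated error rate. The evidence is the contrast in wording between the primary question and the other questions, set against the section's general multilevel rules.

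The size depends on how the contradiction is resolved. A one-wave regression is valid but loses about 27% of children at T4 or 34% at T5, given the plan's 10% loss per interval. A pooled regression without a child level would reject a true null in about 17% to 32% of trials, given assumed correlations of 0.3 to 0.8. The general multilevel statements suggest that a multilevel primary model may have been intended; if so, the primary-question sentence is wrong as written. It should be corrected before the data are analysed.

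**What to change.** In Analyses, replace the regression named for the primary question with the two-level model used for the other questions: assessments within children, with a random intercept per child. Add Time and Group-by-Time, and define the primary effect as the group difference at the post-intervention assessment, not an average over T1 to T5. If Time stays coded 0 to 4, the Group coefficient is the difference at T1, so the text should name the contrast or recode Time so that zero is the post-intervention assessment. State that the standard error and 95% interval come from this model.

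The cost is about one sentence of wording and slightly more analysis work, with no new data. The interval will be wider than a pooled regression would give. A single named time point would also give a valid test, but the at-least-one-wave rule would then have to be withdrawn for the primary analysis.

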**Fig. 2 Fig2:**
[figure not shown]
Flow diagram of ‘Learn to Dare!’ study

Parents (and children, when they are 12 or older) send a signed informed consent form to our university, after which they receive an automatically generated e-mail with their account information. With this account, the children have access to the screening questionnaire on the platform. The authors that will be responsible for data analyses do not have access to the accounts and are completely blinded from participants’ information.

We use the Youth Anxiety Measure for DSM-5 (YAM-5, [54, 55]) as a screening tool and to measure the development of anxiety over time. When completing the YAM-5, children also fill in their demographic features. Children who score in the highest quartile are labelled as high-anxious. We use different cut-offs for boys and girls in order to increase the chance of a proportional influx of boys and girls. All other children are excluded and receive a message that they are not severely anxious, and that the program is not intended to suit their level of anxiety. These children receive links to general anxiety websites for children.

Consecutively, the high-anxious children are invited by e-mail to book a date for a diagnostic interview. The diagnostic interview Structured Clinical Interview for DSM-5 Disorders for Children (SCID, [56]) is performed by telephone with a trained interviewer. If the SCID shows that a child suffers from a severe anxiety disorder other than specific phobias, the child is excluded from the study. In this case, the first author does get access to the accounts of the participants (unblinding) as the parents are contacted by phone. Parents are advised by the first author to seek help for their child at a local mental health care institution.

The study concerns a randomized controlled trial (RCT). Within the ‘Learn to Dare!’ platform, the included high-anxious children are automatically randomized to the intervention group or to the waitlist control group. Children in the waitlist control group can participate in the intervention too after the last assessment point. We apply block randomization with child’s age and sex as strata. If children are randomized to the intervention group, they are assigned personal trainer who helps them during the training. The intervention and assessments are aimed at the children only.

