Children in both groups perform the same assessments, which are all online within the ‘Learn to Dare!’ platform. Assessment points are aligned with the mediators, which means they take place before and after exposure and cognitive restructuring is offered to the children. At every assessment point child anxiety, avoidance behavior and dysfunctional cognitions are measured. The assessments are embedded in the intervention program, and take place after session 1 (after psycho-education and before the child’s expectancies are made explicit), after session 3 (before the start of actual exposures), after session 5 (before the start of cognitive restructuring), and at the end of the training. Control children receive automatically generated e-mails to notify them they have to complete an assessment. A follow-up assessment takes place 12 weeks after the last session. Both the intervention children and control children receive an automatically generated e-mail to notify they have to complete this assessment. At the follow-up assessment, the children take part in the diagnostic interview again. If children do not complete an assessment or intervention session, they will receive automatically generated reminders by e-mail twice. A research assistant also monitors the progress of the children and of the interviewers and trainers.

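### The printed primary efficacy model names no wave and has no time term and no pre-randomisation YAM-5, which conflicts with the repeated-measures design that the article describes

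*Protocol article*

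**What the plan says.** The Analyses section introduces the primary analysis as follows: "To test the primary research question, we will use regression model with the outcome Anxiety Level (AL) as dependent variable and condition (LTD vs WL)". It then prints the equation: "Model: AL = b0 + b1*Group + b2*Sex + b3*LC + b4*Group*Sex + b5*Condition*LC". LC is the age category. The wave of AL is not given.

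The next sentence turns to other questions: "To test the moderation and mediation models, we will use multilevel analysis". There the waves are set out: "The five assessments (T1,T2,T3,T4,T5) will be the lowest level, the children the second level". Time is introduced in that part, for the mediation and moderation models. No printed formula contains a Group-by-Time term.

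The opening of the same section is broader. It says that multilevel analysis "is used to answer the various sub-questions", and it describes time as the within-subject factor. Later it says that drop-outs can stay in because multilevel analysis is used, that nothing is imputed, and: "Subjects with at least one wave (time point) with complete data will be used in the analysis".

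The Procedure section says that the YAM-5 serves "as a screening tool and to measure the development of anxiety over time". Only children who pass that screen are randomised. On timing it says: "The assessments are embedded in the intervention program, and take place after session 1". Further assessments follow session 3, session 5, the end of training, and 12 weeks after the last session. These five match T1-T5, so the screening score is in none of the printed models.

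**The concern.** An equation printed term by term is a choice, not a detail left for later, and this one does not carry out the design around it. An analyst could apply it in two ways that exclude each other.

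- **All five waves pooled.** The group coefficient is then a single average over time. It includes T1, which comes before any exposure work, and T2, which the Procedure section also places before exposure.
- **One late wave.** This is a complete-case regression, so the missing-data statement about multilevel analysis does not apply to the primary question.

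The two routes estimate different quantities and can differ by a factor of two or more. Leaving the choice open allows it to be made after the data are seen. In addition, the outcome instrument is recorded before randomisation for every randomised child and is not used, so some precision is given up.

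**Working it through.** **Inputs from the article.** 120 children per arm; 10% random drop-out between measurements (Participants); five waves T1-T5 (Analyses). Two-sided 5% is inferred from the 95% confidence intervals.

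**Assumptions (not in the article).** A medium effect is taken as 0.5 SD at the end of training. Within-child correlation (ICC) is 0.3-0.7. T1 is complete. The group coefficient is read as the effect averaged over sex and age category.

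**The plan's own figure.** The 240 comes from a simulation whose numerical inputs are not printed, so it can be neither reproduced nor refuted. A two-group comparison at 0.5 SD needs 63 per arm for 80% power, or 87 after three intervals of 10% loss (63/0.729) and 97 after four (63/0.656). The excess over these probably reflects the small indirect effects.

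**1. Retention.**
- T4: 0.9³ = 0.729, which is 175 of 240, about 87 per arm.
- T5: 0.9⁴ = 0.656, which is 157 of 240, about 79 per arm.

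**2. Single late wave, no baseline.** SE = √(2/n) and power = Φ(0.5/SE − 1.96).
- T4: SE = √(2/87.5) = 0.151; power 91%.
- T5: SE = √(2/78.7) = 0.159; power 88%.

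**3. All waves pooled, no time term.** The shares of children whose last wave is T1, T2, T3, T4 or T5 are 0.100, 0.090, 0.081, 0.073 and 0.656. A child with m waves has weight w = m/(1 + (m−1)·ICC). The expected coefficient is Σ(share × w × mean effect over the first m waves) / Σ(share × w), and SE = √(2/(120 × Σ(share × w))).

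Example: ICC 0.5, effects 0, 0, 0.3, 0.5, 0.5 SD.
- The weights are 1, 1.333, 1.5, 1.6 and 1.667, so Σ(share × w) = 1.552.
- The mean effects over the first 1 to 5 waves are 0, 0, 0.10, 0.20 and 0.26, so the numerator is 0.320.
- Coefficient = 0.320/1.552 = 0.206; SE = √(2/(120 × 1.552)) = 0.104; power = Φ(0.206/0.104 − 1.96) = 51%.

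| Assumed effect at T1-T5 (SD) | ICC | Coefficient (SD) | SE | Power |
|---|---|---|---|---|
| 0, 0, 0.3, 0.5, 0.5 | 0.3 | 0.213 | 0.090 | 65% |
| same | 0.5 | 0.206 | 0.104 | 51% |
| same | 0.7 | 0.200 | 0.115 | 42% |
| 0, 0.17, 0.33, 0.5, 0.5 | 0.3 | 0.257 | 0.090 | 81% |
| same | 0.5 | 0.250 | 0.104 | 67% |
| same | 0.7 | 0.244 | 0.115 | 57% |

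The second profile allows for a conflict in the article. The Procedure section places T2, after session 3, before exposures start. The Intervention section puts the first experiment within the session 3 sequence. The two must be reconciled. T1 precedes exposure on either account. Across both profiles the coefficient is about 40-51% of the end effect (0.200/0.5 to 0.257/0.5).

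**4. Screening YAM-5 as covariate.** The SE is multiplied by √(1 − r²). The article gives no r.
- r = 0.3: factor 0.954, SE 5% smaller.
- r = 0.5: factor 0.866, SE 13% smaller.
- r = 0.7: factor 0.714, SE 29% smaller.

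**The case against.** The strongest reply is that the article condenses a preregistered analysis plan, cited in the Procedure and Data Availability sections and not seen here, which may name the wave and the contrast. The opening of the Analyses section also points to a multilevel analysis with time as a factor, so a repeated-measures primary model may have been intended. This stands in part: the intention is plausible. But the printed equation does not carry it out, and the text that follows attaches multilevel analysis and Time to the mediation and moderation models. Even a multilevel fit of this equation would return one time-averaged difference.

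Several stronger readings are tempting, and the document does not support them.

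- **The primary result is a biased completer analysis.** The text does not settle on a single wave. If one is used, the plan's own assumption of random drop-out leaves the estimate unbiased, and power stays above 80% at 0.5 SD. Bias arises only if that assumption fails.
- **The trial suffers both dilution and loss of children.** The two readings are alternatives and cannot both apply.
- **The best covariate is thrown away.** No correlation is documented. Entry is limited to the top YAM-5 quartile, which narrows the range and probably puts r toward the lower end of 0.3-0.7. Omitting a baseline covariate in a randomised trial costs precision, not validity.
- **Children are lost before T1 unequally by arm.** In the intervention arm T1 follows a session, so this is possible. There is no figure for it, and the plan provides reminders and asks children who stop the intervention to complete assessments anyway.

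**Conclusion.** The point holds as a defect in the stated primary model. The equation omits Time, Group-by-Time, a named wave and the pre-randomisation YAM-5, and it does not match the repeated-measures design in the same section.

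Its size depends on the reading. Pooling gives an expected coefficient of about 0.20-0.26 SD and power of about 42-81%. One late wave gives 88-91% power with 73% or 66% of children. All of these assume 0.5 SD at the end of training; the pooled figures also depend on the assumed effect profile and an ICC of 0.3-0.7. Some dilution occurs under any profile that rises over time.

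This should be fixed, but it does not invalidate the trial. A reader might infer that 240 children are too few; the check does not show that, because the simulation inputs are not printed.

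**What to change.** Make the primary analysis a mixed model for YAM-5 at T1-T5 with group by categorical wave, sex, age category and the screening YAM-5. The screening score can enter as a covariate, or as a wave 0 with the arms constrained equal. Name one primary contrast, for example the group difference at T4 (end of training). Align the missing-data paragraph with this model, and reconcile the two descriptions of session 3 so that the status of T2 is clear.

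With screening as wave 0, all randomised children are formally in the model, but those with no later score add almost nothing to the group contrast.

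The cost is analysis wording only: the screening YAM-5 is already collected for every randomised child, and no visit, measure or sample size changes.
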